#### **4.4 Procedures**

Patients will be randomly allocated to one of the treatment sequences (A, B, C, D, E or F, Figure 1) and will start treatment with either the branded warfarin sodium or with one of the two generic versions available in the Brazilian market in August 2013. The first phase of the study will last 21 days. During this period, the patient, who had already been using warfarin, will start the randomly allocated treatment that will also be used in the second phase of the clinical trial. The use of the same treatment in phases one and two aims to avoid the carry-over effect without the interruption of anticoagulation treatment, which would be ethically unacceptable. The duration of three weeks for this phase is equivalent to about seven warfarin half-lives (38), the washout time for elimination of this drug. The duration of this phase will allow us to ensure that the formulation of warfarin used previously does not interfere with the results of the trial.

The second, third and fourth phases of the study will last 28 days each, in order to allow more weekly measurements to assess the effect of therapy with each of the formulations. In the second phase the patients will continue with the treatment started in phase one, and in the third and fourth phases will occur the change of warfarins according to the predetermined sequences for each group.

##### **4.4.1 Randomization**

The randomization sequence will be generated by an independent investigator ([name]) using a random number table created with the Microsoft Excel software. The independent investigator ([name]) will be responsible for maintaining the confidentiality of the randomization sequence until the data analysis phase, assigning to the medication the initials of the patient and an alphanumeric code that will correlate with the formulation of the warfarin used. The medication will then be dispensed by the principal investigator ([name]) in opaque and identical sealed packages.

##### **4.4.2 Intervention**

Patients will receive, according to the study phase, the branded warfarin sodium (Marevan, manufactured by Farmoquímica, Brazil) or one of the generic drugs (one manufactured by União Química Farmacêutica Nacional S/A and the other manufactured by Laboratório Teuto Brasileiro S/A, Brazil) available in the Brazilian market in August 2013.

The prescription of the drug will be issued in the generic drug name, thus allowing the patient to receive both the branded and the generic medications. The tablets available on the market have a similar appearance to each other and the dispensation will be carried out by the PI in the outpatient clinic. Opaque and identical sealed packages for the medication will prevent patients, doctors and the lead investigator from being aware of the warfarin that the patient will use. Patients will receive enough medication to be used in the period between laboratory tests. Afterwards, the returned tablets will be counted with two objectives: to assess and encourage treatment adherence. The dose adjustment will be carried out monthly, or more frequently at medical discretion, if the INR results fall out of the reference range, whose target is maintenance between 2.0 and 3.0.

#### **4.5 Variables and outcomes**

Outcome data will be collected by the principal investigator ([name]). Laboratory tests (INR and TP) and clinical outcomes (thromboembolic events and bleeding) will be assessed twice a month; treatment adherence will be assessed monthly.

##### **4.5.1 Primary outcome**

- Mean INR

The average INR of each patient will be compared when using the different warfarin formulations.

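### Mean INR is the sole basis for equivalence while doses may be changed on that same INR, and no outcome or analysis takes dose into account

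*Protocol*

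**What the plan says.** - Outcome (Protocol 4.5.1): "The average INR of each patient will be compared when using the different warfarin formulations". Section 3 sets the equivalence limit at 0.49 INR units, and 4.6.2 analyses mean INR by paired t-test.
- Dosing (4.4.2): "The dose adjustment will be carried out monthly, or more frequently at medical discretion, if the INR results fall out of the reference range". The INR target is given as "whose target is maintenance between 2.0 and 3.0".
- Phases (4.4): "The second, third and fourth phases of the study will last 28 days each". On switching: "in the third and fourth phases will occur the change of warfarins according to the predetermined sequences for each group". Phase 1 is a 21-day run-in on the first product. It is justified thus: "The duration of three weeks for this phase is equivalent to about seven warfarin half-lives (38), the washout time for elimination of this drug". No run-in is described for phases 3 and 4.
- INR frequency: section 4.4 gives the length of the phases as chosen "in order to allow more weekly measurements to assess the effect of therapy with each of the formulations", whereas 4.5 says that laboratory tests "will be assessed twice a month".
- Dose: it is absent from the specific objectives (2.2), the outcomes (4.5.1 and 4.5.2) and the analyses (4.6.2). Returned tablets are counted, but only for adherence. The Protocol does not say that the prescribed dose is recorded for analysis.

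**The concern.** INR is both the yardstick and the quantity that treatment steers. If one product is stronger, more of its INRs leave the target range, doses come down, and part of the product effect moves out of the INR and into the dose. PT and TTR pass through the same adjustment, so no laboratory outcome isolates what was compensated by dose.

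In a superiority trial this would cost power. In an equivalence trial, a bias towards no difference favours the conclusion under test. Similar mean INRs could then show that titration worked as well as that the products are alike, and the planned analyses could not separate the two.

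**Working it through.** **Planning figures.** With SD 0.29, difference 0.49, two-sided 5% and 90% power (4.6.1), n = 2 × (1.960 + 1.282)² × (0.29/0.49)² = 7.36, so 8 per group and 8 × 6 = 48, as stated. The sample size does not bear on this point, but the mean of 2.45 and SD of 0.29 are used below.

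**How often would a dose change be prompted?** Assume single INRs are normal with SD 0.29. The share outside 2.0 to 3.0 is:
- mean 2.45: 8.9%
- mean 2.45 + 0.49 = 2.94: 41.9%
- mean 2.45 − 0.49 = 1.96: 55.5%

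Dose changes would therefore cluster where the products differ.

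**When would the change fall?** The measured phases start on days 21, 49 and 77. A 28-day clock started at enrolment reaches days 28, 56 and 84, which is day 7 of each measured phase. A clock started with each phase reaches the phase boundary instead. The text allows both, and more frequent changes at discretion.

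**Effect on mean INR.** Two-period simulation, 200,000 patients per scenario. Assumptions: INRs on days 14 and 28; SD 0.29 with variance split equally between and within patients; a 3-day half-life; an out-of-range INR prompts a change that removes 50% or 100% of its deviation from 2.5. Cells show the observed difference at 50% / 100% correction.

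| Adjustment | true 0.49 | true 0.60 | true 0.80 |
|---|---|---|---|
| none | 0.480 / 0.480 | 0.587 / 0.588 | 0.783 / 0.784 |
| phase end only | 0.518 / 0.529 | 0.636 / 0.639 | 0.848 / 0.820 |
| mid-phase only | 0.476 / 0.427 | 0.581 / 0.504 | 0.765 / 0.633 |
| both | 0.471 / 0.362 | 0.562 / 0.403 | 0.715 / 0.458 |

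The largest loss in the table is 1 − 0.458/0.80 = 43%. With weekly INRs and one full correction on day 7, a true 0.80 read 0.37, a loss of 1 − 0.37/0.80 = 54%.

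A second model used six treatment orders and a product 20% stronger. With INR proportional to dose, the true difference is 2.45 × 0.2 = 0.49. With adjustment allowed within phases it read 0.456 and 0.417 (10% and 15% dose steps) and 0.287 (re-titration to 2.5). With a dose-response exponent of 1.5, the true difference is 2.45 × (1.2^1.5 − 1) = 0.77, and it read 0.633, 0.536 and 0.410. With phase-end adjustment only, 0.49 read 0.51 to 0.53 and 0.77 read 0.75 to 0.81.

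**Which dose analysis would show it?** Full compensation for a product 20% stronger would give a dose ratio of 1/1.2 = 0.83. The simulated ratio stayed between 0.93 and 1.02, so mean dose alone reveals little. Dose-adjusted INR recovered a ratio of 1.20 under every timing when the dose response was correctly specified, as it must by construction. A wrong exponent matters. If the true exponent is 1, the assumed one 1.5 and the dose ratio 0.93, the adjusted INR ratio is 1.2 × 0.93^(−0.5) = 1.24, against 1.2 × 0.93 = 1.12 unadjusted.

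**Missing run-in.** The implied half-life is 21/7 = 3 days, and the residual of the old product is 2^(−t/3): 0.198 on day 7, 0.039 on day 14, 0.008 on day 21 and 0.002 on day 28. The mean residual is 2.0% for INRs on days 14 and 28, and 6.2% for weekly INRs. A true 0.49 then reads 0.480 or 0.460. This covers drug elimination only; the Protocol gives no figure for any further lag in the INR response.

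**The case against.** The trial asks whether substitution is effective and safe in patients (1.1), so INR under usual management is a legitimate outcome. Adjustment is conditional on an out-of-range INR and monthly by default. If the month coincides with the 28-day phase, nothing is corrected within it and the bias disappears or reverses. TTR records out-of-range time before any correction. All of this stands, and it is why the primary endpoint need not change. It does not remove the point: discretionary mid-phase changes are expressly allowed, the monthly clock is not tied to the phases, and TTR is a secondary outcome with no part in the equivalence limit.

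A reader might infer three stronger things that the Protocol does not support:
- *That dilution is certain.* It depends on timing and size of adjustment, which are not stated. With 10% or 15% steps, a true 0.77 still read outside 0.49; only full re-titration brought it inside.
- *That INRs are counted straight after each switch, so old product seriously contaminates phases 3 and 4.* The Protocol does not say which INRs enter the mean, and a statistical analysis plan could set a window. At the implied half-life the effect is 2% to 6%.
- *That dose should be a second primary endpoint, or that only INRs from day 21 of each phase should be used.* The dose ratio responds weakly, and the Protocol offers no basis for a limit. Late INRs are the most titrated: in the re-titration run the difference was 0.287 for the phase mean and 0.096 at the last visit.

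**Conclusion.** The point holds in limited form. Mean INR alone carries the equivalence claim, the dose may be changed on that INR within the measured phases, and nothing in the Protocol uses dose. The possible understatement runs from nothing to about half with mid-phase changes; with phase-end changes the difference is mostly kept or slightly enlarged. In the worst case, full correction at every visit, differences of 0.60 to 0.80 appear inside the 0.49 limit. These sizes rest on assumed visit days, variance split, dose response and correction rules, none of which the Protocol gives.

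The conflict over INR frequency is plain on the text. It matters here because it changes both the number of INRs per phase and the opportunities to adjust. The missing run-in in phases 3 and 4 sits awkwardly with the three-week washout argument, but is minor.

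**What to change.** Leave the dosing rules and the primary endpoint unchanged.

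1. Record the prescribed daily dose in effect at each INR.
2. Pre-specify two supportive analyses: (a) mean daily dose by product and phase; (b) a dose-adjusted INR comparison, using log INR with log dose as an offset or the INR/dose ratio, repeated over a range of assumed dose responses.
3. Add a sensitivity analysis of mean INR with period and previous-product terms. This also addresses doses set under one product and carried into the next, and the absent run-in.
4. State that the equivalence conclusion will be qualified if INR and dose-adjusted INR disagree.
5. Reconcile the INR frequency in 4.4 with that in 4.5, and state how dose adjustment in 4.4.2 falls relative to the phase boundaries in 4.4.

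Cost: one more item recorded at each visit, a few lines of text and a small amount of analysis. The downside is that the dose-adjusted comparison depends on an assumed dose response, which is why it should be varied and kept supportive.

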##### **4.5.2 Secondary outcomes**

- Mean PT

The mean PT will be evaluated in the same way as the INR.

- Time within the therapeutic range (TTR).

This ratio is calculated for each patient by the percentage of person-time within the therapeutic range of 2.0 and 3.0 divided by the total person-time contribution by that same individual (39).

- Frequency of thromboembolic events

It includes ischemic stroke (differentiated from hemorrhagic stroke by tomography) and thromboembolism on the viscera or extremities (diagnosed by acute symptoms and relevant diagnostic tests) (40).

- Frequency of bleedings

Bleeding events will be classified as major or minor bleedings:

- Major bleeding: intracranial bleeding, fatal bleeding, blood loss resulting in a decrease greater than or equal to 2.0 g / L of serum hemoglobin, bleeding requiring transfusion, bleeding in sensitive areas such as the retina or pericardium.
- Minor bleeding: all other bleeding (33).

- Adherence to treatment

Adherence will be calculated by the amount of tablets returned by the patient.

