#### **4.6 Statistical Method**

##### **4.6.1 Sample size**

At least 48 patients (8 in each group) will be needed in order to identify a clinically significant difference of 0.49 in the INR, considering a mean INR of 2.45 with standard deviation of 0.29, data reported for a branded warfarin in a published study (13). The sample was calculated based on the mean INR outcome, using the statistical method for quantitative outcomes (41) assuming  $\alpha = 5\%$  and  $\beta = 10\%$ , which result in a power of 90%. We plan to recruit 60 individuals (10 in each group) to compensate for possible dropouts or exclusions of patients.

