##### **4.6.2 Statistical analysis**

All statistical analyzes will have a significance level of 5%. Paired-samples t-tests (also called dependent T-tests) will be used for the outcome of mean INR and PT. Analysis will be performed by protocol for these outcomes i.e., data from patients who start treatment with any drugs that interact with warfarin as previously defined (list in Annex II) will be excluded from the final analysis.

The dichotomous outcomes (TTR, thromboembolic events, bleeding) will be analyzed by McNemar's test. Exploratory analyzes for patient subgroups are not planned. The dichotomous variables will be analyzed by intention to treat, considering the missing data as an unfavorable outcome, in which case a sensitivity analysis will be carried out to assess the robustness of the result.

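### The haemoglobin criterion for major bleeding, a fall of 2.0 g/L (0.2 g/dL), is out of scale with the rest of its list and is most plausibly a g/L for g/dL slip

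*Protocol*

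**What the plan says.** Protocol section 4.5.2 lists the frequency of bleedings among the secondary outcomes and sets up two classes: "Bleeding events will be classified as major or minor bleedings". One of the criteria for the major class is "blood loss resulting in a decrease greater than or equal to 2.0 g / L of serum hemoglobin". The others are intracranial bleeding, fatal bleeding, bleeding that needs a transfusion, and bleeding at critical sites. Any bleed that meets none of these is minor. Reference 33 is cited at the end of the definition.

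The g/L unit appears only here. No other section restates the threshold, gives it in another unit, or adds a time window, a confirmatory reading or a reference value.

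On measurement, section 4.5 says: "Laboratory tests (INR and TP) and clinical outcomes (thromboembolic events and bleeding) will be assessed twice a month". Haemoglobin is not among the tests named. On analysis, section 4.6.2 says: "The dichotomous outcomes (TTR, thromboembolic events, bleeding) will be analyzed by McNemar's test". It does not say whether major bleeding is tested separately from all bleeding.

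**The concern.** The criteria in the list should be of broadly similar gravity, since meeting any one of them makes a bleed major. A haemoglobin fall of 0.2 g/dL is not comparable with a fatal or intracranial bleed or with a need for transfusion. It is also small enough to be met by ordinary differences between two readings.

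Because the minor class is simply the remainder, this threshold moves the boundary between the classes directly. If it is followed as written, a nosebleed or bruise in a patient who happens to have two haemoglobin values could be reported as a major bleed. The counts of major bleeding by formulation would then mix serious events with trivial ones, in a trial whose stated purpose includes the safety of substitution.

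The phrase also refers to serum haemoglobin. Blood loss is judged on haemoglobin in whole blood, because serum contains no red cells. That is a wording error, but it sits in the same phrase and makes a drafting slip there more likely.

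**Working it through.** **Inputs.** The threshold of 2.0 g/L is from section 4.5.2. The protocol gives neither a baseline haemoglobin nor a measure of its variability, so both are assumed over a range: baseline 120, 135 and 150 g/L, and total per-reading coefficient of variation (CV) from 1% to 4%.

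**Step 1, unit.** 1 g/dL = 10 g/L, so 2.0 g/L = 0.2 g/dL, and 2.0 g/dL = 20 g/L.

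**Step 2, size relative to baseline.**
- 2.0 g/L: 2/150 = 1.3%, 2/135 = 1.5%, 2/120 = 1.7%.
- 20 g/L: 20/150 = 13%, 20/135 = 15%, 20/120 = 17%.

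The second row is of an order that fits the other criteria in the list. The first is not.

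**Step 3, comparison with reading-to-reading variation.** For two readings with no true change between them, taking normal errors:
- SD of the difference = √2 × CV × baseline
- 95% limit for a change = 1.96 × SD of the difference
- P(apparent fall ≥ t) = 1 − Φ(t / SD of the difference)

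| Baseline (g/L) | CV | SD of difference (g/L) | 95% limit (g/L) | P(fall ≥ 2.0 g/L) | P(fall ≥ 20 g/L) |
|---|---|---|---|---|---|
| 120 | 1% | 1.70 | 3.3 | 0.119 | <0.0001 |
| 135 | 2% | 3.82 | 7.5 | 0.300 | <0.0001 |
| 135 | 3% | 5.73 | 11.2 | 0.363 | 0.0002 |
| 150 | 4% | 8.49 | 16.6 | 0.407 | 0.0092 |

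Worked line: at 135 g/L and 3%, the SD is 1.414 × 0.03 × 135 = 5.73. Then 2/5.73 = 0.349 and 1 − Φ(0.349) = 0.363.

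The first and last rows are the extremes of the range tried. The 2.0 g/L threshold is below the 95% limit in every case, even at a CV of 1%. The chance of an apparent fall that large is about 12–41% per pair, against at most 0.9% for 20 g/L.

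**Step 4, what the threshold does not touch.** The sample size in section 4.6.1 rests only on INR inputs: a difference of 0.49 and an SD of 0.29. It reproduces with the usual two-mean formula at two-sided 5% and 90% power: 2 × (1.96 + 1.282)² × 0.29² / 0.49² = 7.4, rounded up to 8 per group, and 6 × 8 = 48. Haemoglobin plays no part in it. A McNemar comparison of any bleeding, major or minor, is also unchanged, because moving a bleed between classes leaves the total the same.

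**The case against.** Several points on the other side have weight.

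- **The slip is inferred.** No other figure in the protocol conflicts with g/L, and reference 33 is not at hand. This stands: the replacement value has to be conditional on checking the source.
- **The percentages are easily over-read.** A reader might infer that about a third or more of all patients who bleed would be called major by chance. The protocol does not support that. The figures apply to pairs of readings with no true change, under assumed variation. Haemoglobin is not scheduled, so the share of bleeds with such pairs is unknown and may be small.
- **The criterion is not purely numerical.** The definition requires that the blood loss caused the fall, so a chance difference between readings does not strictly qualify. This stands as far as it goes, but the protocol gives no rule for telling a real 2 g/L loss from noise. Moreover, a real fall of 1.3–1.7% is itself small beside the other criteria, so the problem does not depend on noise.
- **The reach is limited.** A reader might infer that the trial's main safety result is compromised or that real differences are hidden. Bleeding is one of several secondary outcomes that the protocol does not rank, and section 4.6.2 names no separate test of major bleeding.
- **Serum for blood is editorial.** Nothing suggests that free haemoglobin in serum would actually be measured. It should be corrected in passing and carries no weight of its own.

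None of this makes 2.0 g/L a sensible companion to fatal and intracranial bleeding.

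**Conclusion.** The definition is wrong in scale as written. A fall of 2.0 g/L is 0.2 g/dL, a tenth of the threshold if g/dL was meant, and no other text in the protocol corrects it. Followed literally, it allows trivial bleeds with haemoglobin readings to be labelled major and so blurs the major/minor split of a secondary safety outcome.

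The unit conversion needs no assumption. The percentage of baseline assumes a haemoglobin of 120–150 g/L, and the chance figures further assume a per-reading CV of 1–4% and apply only where paired readings exist. That the intended unit was g/dL is the most plausible reading but is not established by the protocol. The number of bleeds that would actually be misclassified cannot be derived from it.

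The point is worth correcting because the change is small and the definition will be applied literally. It is not a threat to the trial's primary conclusion.

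**What to change.** 1. Verify the unit of the haemoglobin criterion against reference 33.
2. If the slip is confirmed, correct the outcome definition in section 4.5.2 to a fall of at least 2.0 g/dL (20 g/L) in blood haemoglobin attributable to the bleed, with blood replacing serum.
3. Make the correction before any bleed is classified as major or minor, so that one definition applies to every formulation.

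The cost is a one-line edit to an outcome definition. The downside is that fewer events will be labelled major. The edit does not supply haemoglobin values that are not collected: with no scheduled measurement, the criterion will still apply only to bleeds for which readings happen to exist.

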#### **4.6 Statistical Method**

##### **4.6.1 Sample size**

At least 48 patients (8 in each group) will be needed in order to identify a clinically significant difference of 0.49 in the INR, considering a mean INR of 2.45 with standard deviation of 0.29, data reported for a branded warfarin in a published study (13). The sample was calculated based on the mean INR outcome, using the statistical method for quantitative outcomes (41) assuming  $\alpha = 5\%$  and  $\beta = 10\%$ , which result in a power of 90%. We plan to recruit 60 individuals (10 in each group) to compensate for possible dropouts or exclusions of patients.

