### 3. Hypothesis

The comparison of the mean INR between branded and generic warfarins is within the limit of 0.49 (two-sided, with a significance level of 5%) demonstrating therapeutic equivalence between them.

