## 4. Methods

#### 4.1 Type of study

Randomized crossover controlled trial containing six treatment sequences and divided into four phases with different durations (Figure 1). The study is registered in [www.clinicaltrials.gov](http://www.clinicaltrials.gov) under the identification NCT02017197 and also has the Universal Trial Number (UTN) U1111-1155-4833.

[figure not shown]

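### Section 4.6.1 multiplies a two-arm parallel-group size by six sequences, so neither the need for 48 patients nor the 90% power describes this paired crossover; the error is conservative

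*Protocol*

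**What the plan says.** Protocol section 4.6.1 states: "At least 48 patients (8 in each group) will be needed in order to identify a clinically significant difference of 0.49 in the INR". Its inputs are a mean INR of 2.45 and an SD of 0.29, both taken from a published study of a branded warfarin, with alpha 5% and beta 10%. It cites a general method for quantitative outcomes. Recruitment is set at 60 (10 per group) to allow for losses.

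The rest of the protocol describes a different comparison:

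- Section 4.1: "Randomized crossover controlled trial containing six treatment sequences".
- Section 4.5.1: the primary outcome compares each patient's mean INR across the products.
- Section 4.6.2: "Paired-samples t-tests (also called dependent T-tests) will be used" for mean INR and PT.
- Section 3: the hypothesis is equivalence. The difference between branded and generic products "is within the limit of 0.49 (two-sided, with a significance level of 5"%).

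Section 4.4.2 gives the INR reference range, "whose target is maintenance between 2.0 and 3.0".

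**The concern.** Section 4.6.1 treats the six sequences as if they were the groups being compared. In this crossover every completing patient takes all three products and contributes to every product comparison. The precision therefore depends on the total number of patients and on the SD of the within-patient difference. The protocol gives neither that SD nor a correlation from which to derive it.

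The aim is also mismatched. Section 4.6.1 sizes the trial "in order to identify a clinically significant difference of 0.49 in the INR", while section 3 makes the same 0.49 the bound within which products count as equivalent. Power to detect a difference is not power to show equivalence.

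At stake is the stated basis for the trial's size. A reader relying on section 4.6.1 would think that 48 is the minimum and that the trial has a 10% chance of failing its aim at 0.49. Neither follows from the planned analysis.

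**Working it through.** **Inputs.** Difference or limit 0.49, SD 0.29, mean 2.45, power 90%, N = 48 (section 4.6.1). Alpha 0.05, two-sided (sections 3 and 4.6.2). Target range 2.0 to 3.0 (section 4.4.2). Assumed, because the protocol gives no figure: the within-patient correlation rho, or directly the SD of within-patient differences.

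**1. Reproducing the plan's figure.** For two independent arms and a test for a difference:

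n per arm = 2 × [0.29 × (1.960 + 1.282) / 0.49]² = 7.36, rounded up to 8.

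8 × 6 sequences = 48, an exact match.

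The same 7.36 arises from a paired formula with zero correlation, since the variance of the difference is then 2 × 0.29². On that reading 8 would be the total number of patients. Multiplying by six is unjustified either way.

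**2. SD of the paired difference on the plan's SD.** SD_d = 0.29 × √(2(1 − rho)). This gives 0.41 at rho 0, 0.29 at rho 0.5 and 0.13 at rho 0.9.

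**3. Total patients needed for 90% power at 0.49, per pair of products.** The paired t-test uses the noncentral t distribution. Two one-sided tests (TOST) are computed at a true difference of 0.

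| rho | Paired t-test | TOST, one-sided 0.05 | TOST, one-sided 0.025 |
|---|---|---|---|
| 0 | 10 | 10 | 12 |
| 0.5 | 6 | 6 | 7 |

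**4. Power with N = 48.** For rho from 0 to 0.9, both the paired t-test at a difference of 0.49 and TOST within ±0.49 have power above 99.9%.

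**5. Larger assumed SDs.** The standard error is SE = SD_d/√48, and TOST power at a true difference of 0 is approximately 2Φ(0.49/SE − t) − 1. With 47 degrees of freedom, t = 1.678 (one-sided 0.05) or 2.012 (one-sided 0.025).

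- SD_d = 0.8: SE = 0.1155 and 0.49/SE = 4.24. Power is about 99% (one-sided 0.05) or 97% (0.025).
- SD_d = 1.0: SE = 0.1443 and 0.49/SE = 3.39. Power is about 91% or 83%.

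So with 48 patients the 90% figure would be roughly right only if the SD of differences were about 1.0, which is about 2.4 times the zero-correlation value (1.0/0.41).

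**6. Position of the limit.** 0.49/2.45 = 0.20, so the limit is 20% of the reference mean. 2.45 − 0.49 = 1.96, which is below 2.0. 2.45 + 0.49 = 2.94, which is inside the range.

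**The case against.** The main reply is that nothing is endangered. On the plan's own SD the trial has more power than it claims, no comparison is short of patients, and no more need be recruited. That stands, and it makes this an error of justification rather than of size. Nor does using a difference formula instead of an equivalence formula move the number much: parallel-group TOST at one-sided 0.05 gives 7.58, also 8 per arm. The errors with consequences are the multiplication by six and the missing SD of differences.

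A second reply is that the surplus of precision is itself unproven. Section 4.5 has INR assessed twice a month, so a 28-day mean may rest on about two readings and vary more than 0.29 suggests. Exclusions for interacting drugs (section 4.6.2) and for a phase-one TTR below 70% (section 4.3.2) could take the evaluable number below 48. This stands too. It is why a corrected section should show a range of SDs and not replace 90% with another single figure.

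A reader might infer from the 1.96 edge that a product leaving the average patient below range would be declared equivalent. The documents do not support that. Only true means from 1.96 to 2.00 lie both inside the limit and below 2.0, and this strip depends on the borrowed mean: with a brand mean of 2.50 the edge is 2.01 and the strip is gone. Under a confidence-interval rule, a product exactly at the limit would pass only 2.5 to 5% of the time.

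A reader might also want the limit tightened because precision seems available. An equivalence limit needs clinical grounds, and the documents offer none for a narrower one.

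**Conclusion.** Section 4.6.1 is wrong as written. That the 8 came from a two-arm formula is inferred from exact reproduction, since the protocol names only a general method. But no reading of that formula justifies multiplying by the number of sequences. The claims that at least 48 patients are needed and that they give 90% power do not describe a paired crossover analysis of equivalence.

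The direction of the error is conservative, and the conclusion should not be read as saying the trial is too small. The size of the misstatement rests on the borrowed SD of 0.29, an assumed correlation, a true difference of 0 for the equivalence figures, 48 evaluable patients, and power taken one pair of products at a time.

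The position of the lower edge of the limit is a secondary point. It calls for a reason from the sponsor and is not evidence that 0.49 is wrong.

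**What to change.** Keep 48 evaluable and 60 recruited patients. In section 4.6.1:

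- Remove the statement that 8 per sequence are needed for 90% power.
- State instead the power of the paired equivalence analysis within ±0.49 at N = 48, naming the one-sided level used.
- Give that power over an explicit assumed range for the SD of within-patient differences, for example from 0.29 to 1.0, and say where the range comes from.
- Align the wording with section 3, so that 0.49 is described as an equivalence limit and not as a difference to be detected.

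Separately, the sponsor should record a clinical justification for 0.49 before unblinding, acknowledging that with a reference mean of 2.45 its lower edge is 1.96.

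The cost is a short amendment, with no added patients, visits or measurements.
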